# Study protocol of a multicenter, randomized, non-inferiority, open-label study investigating the efficacy of a fixed-dose combination regimen of dapagliflozin/metformin versus co-administered dual therapy based on glycemic control, satisfaction and adherence in patients with newly diagnosed type 2 diabetes mellitus

**DOI:** 10.3389/fendo.2025.1690339

**Published:** 2025-11-04

**Keywords:** T2DM, newly diagnosed, dapagliflozin/metformin, FDC, co-administered dual therapy

## Abstract

**Introduction:**

The combination of dapagliflozin and metformin is commonly used as an initial therapy for patients with type 2 diabetes mellitus (T2DM) with high glycated hemoglobin (HbA1c) levels. Although bioequivalence has been established for the fixed-dose combination (FDC) of dapagliflozin/metformin extended-release (XR) compared to the co-administration of dapagliflozin and metformin XR, it remains uncertain whether the efficacy of dapagliflozin/metformin FDC is comparable to that of co-administration. Additionally, it is still unclear whether fixed-dose combinations offer advantages in terms of patient adherence and satisfaction. This study aims to compare the dapagliflozin/metformin XR FDC with co-administration of dapagliflozin and metformin XR for efficacy in terms of glycemic control, patient satisfaction, quality of life and adherence in Chinese patients with newly diagnosed T2DM.

**Methods and analysis:**

This multicenter, randomized, non-inferiority, open-label clinical trial enrolled 632 patients with T2DM (HbA1c 7.5–10%) in 35 research centers in China. After enrollment, the patients will be randomly assigned to receive either FDC treatment (10 mg dapagliflozin and 1000 mg metformin XR) or co-administered 10 mg dapagliflozin and 1000 mg metformin XR tablets for 24 weeks. The primary endpoint was the change in HbA1c level from baseline after 24 weeks of treatment. Secondary endpoints included the proportion of patients achieving HbA1c below 7.0%, absolute changes in fasting plasma glucose and postprandial glucose from baseline to week 24, the difference in patient satisfaction measured with the diabetes treatment satisfaction questionnaire, medication usage measured with adherence to refills and medications scale for diabetes between the two groups at week 24, change from baseline in diabetes quality of life questionnaire score at week 12 and week 24, and safety. Continuous glucose monitoring will also be used to evaluate the benefits of FDC compared with co-administration on glycemic variability.

**Discussion:**

This study, as the first of its kind, will provide comparative data on the efficacy of the dapagliflozin/metformin XR FDC and co-administration of dapagliflozin and metformin XR in terms of glycemic control, patient satisfaction, quality of life and adherence. These data will help clinicians make more informed decisions for patients with type 2 diabetes and may improve medication burden, treatment adherence, and satisfaction.

## Introduction

1

The global prevalence of diabetes poses a significant threat to public health, with China having the highest number of patients with diabetes worldwide. From 2015 to 2017, the prevalence of diabetes among adults in China was 12.8% (1). Long-term blood glucose control is fundamental for diabetes management, and it is important to focus on cardiovascular and renal protection during the treatment process (2).

Metformin has firmly established itself as a cornerstone in the treatment of type 2 diabetes mellitus (T2DM) and remains the first-line medication in most clinical guidelines (3). It effectively lowers blood glucose by reducing hepatic glucose output and improving peripheral insulin resistance. It has benefits such as weight reduction, reduced risk of cardiovascular diseases associated with T2DM, synergistic effects in combination therapy, a good safety profile, and is cost-effective and widely available (3, 4). Sodium-glucose cotransporter 2 (SGLT2) inhibitors, a class of oral antidiabetic agents that have gained widespread application and have been consistently recommended by guidelines in recent years, include dapagliflozin, empagliflozin, canagliflozin, and ertugliflozin (5). These agents lower blood glucose levels by inhibiting SGLT2 in the proximal renal tubules, blocking glucose reabsorption, and promoting urinary glucose excretion (6). In addition to their glucose-lowering effects, SGLT2 inhibitors confer important non-glycemic benefits including renal hemodynamic regulation, decreased urinary protein excretion, blood pressure reduction, and weight loss (7). These non-glycemic pathways have a positive effect on patient treatment, with multiple large-scale clinical trials demonstrating the efficacy of SGLT2 inhibitors in reducing the risk of major adverse cardiovascular events, cardiovascular death, myocardial infarction, heart failure hospitalization, and all-cause mortality, as well as improving renal outcomes in T2DM patients with cardiovascular disease or at high cardiovascular risk (8–11). In addition, SGLT2 inhibitors have been shown to reduce cardiorenal and cardiovascular risks in patients with chronic kidney disease or heart failure, regardless of the presence or absence of diabetes (12, 13).

Glycemic control in patients with diabetes typically requires combination therapies. Studies have shown that initial combination therapy could achieve faster glycemic control and maintain its effects for a longer duration than sequential add‐on therapy (14, 15). The American Diabetes Association (ADA) 2025 Standards of Medical Care in Diabetes and Guidelines for the Prevention and Treatment of Diabetes Mellitus in China (2024 edition) recommended considering initial combination therapy, including fixed-dose combination (FDC), for patients whose glycated hemoglobin (HbA1c) is over 1.5% above the target level (2, 16). Furthermore, combination therapy was recommended for T2DM patients with the HbA1c ≥7.5%, according to the American Association of Clinical Endocrinology (AACE) Consensus Statement (2023) and Metabolic Disease Management Guideline for National Metabolic Management Center (MMC) (17, 18). Nowadays, low adherence to diabetes medication remains an ongoing problem (19). Studies have shown that medication adherence is inversely related to the number of medications (20), and compared to using separate drugs, fixed-dose combination therapy may significantly improve patient adherence to treatment (21). XIGDUO^®^ XR tablet is a FDC of dapagliflozin and metformin hydrochloride XR tablets, and studies have shown bioequivalence between FDC and co-administered dapagliflozin and metformin XR tablets (22). However, it remains uncertain whether the efficacy of dapagliflozin/metformin FDC is comparable to that of co-administration.

Currently, studies comparing FDC to co-administration are generally rare, and there are no head-to-head comparative studies between dapagliflozin/metformin FDC and the co-administration of dapagliflozin and metformin hydrochloride. Additionally, there is no direct evidence of the glycemic control efficacy of the FDC of dapagliflozin 10 mg and metformin XR 1000 mg in patients with T2DM, which is the only available dosage for dapagliflozin/metformin XR FDC in clinical use in China. Therefore, we designed a multicenter, randomized, non-inferiority, open-label clinical trial to compare the effects of dapagliflozin/metformin XR FDC with those of co-administration of dapagliflozin and metformin XR on glycemic control, patient satisfaction, quality of life, adherence, and safety. This study is the first of its kind and has the potential to provide crucial evidence supporting the use of FDCs, including dapagliflozin/metformin XR FDC. Additionally, it may offer valuable insights for clinical practice regarding the selection of treatment regimens for diabetes and improvement of patient adherence.

## Methods and analysis

2

### Study design

2.1

This was a 24-week, multicenter, randomized, non-inferiority, open-label clinical trial designed to compare the FDC regimen of dapagliflozin/metformin XR with dapagliflozin administered alongside metformin XR, based on glycemic control, patient satisfaction, and adherence in Chinese patients with T2DM. The study was conducted at 35 sites in China.

The flowchart of the study is shown in **Figure 1**. After obtaining written informed consent during the screening period, the patients will be assessed for eligibility according to all applicable inclusion and exclusion criteria, and laboratory samples will be collected and submitted. Once the investigator confirms the patient’s eligibility, an HbA1c blood sample will be collected and tested by the central laboratory, with results available within two weeks. Eligible patients will undergo re-evaluation of their inclusion and exclusion criteria based on the test results. Eligible patients will be randomly assigned 1:1 to one of two treatment groups. From week 0, patients in the FDC group will receive treatment with an FDC regimen consisting of 10 mg dapagliflozin and 1000 mg metformin XR tablets for 24 weeks, while the co-administration group will receive 10 mg dapagliflozin tablets and 1000 mg metformin XR tablets for 24 weeks. Among the 632 randomly assigned subjects, the first approximately 179 subjects per group who signed the continuous glucose monitoring (CGM) informed consent will be included in the CGM sub-study, totaling approximately 358 patients. After completing all scheduled tests, examinations, and questionnaires at week 12, participants in the sub-study will undergo CGM (for approximately five days). Follow-up visits will be conducted every 12 weeks (± 5 days) during the treatment period, with an additional follow-up visit at 1 week (± 3 days) after the end of the treatment to evaluate efficacy and safety.

**Figure 1 f1:**
[figure not shown]
Study flowcharts for the main study **(A)** and the exploratory sub-study **(B)**.

### Participants

2.2

To be eligible for the study, participants must be 18 years of age or older at the time of signing the informed consent form and must be capable of signing the written informed consent voluntarily. They had to be newly diagnosed with T2DM (WHO diagnostic criteria 1999), diagnosed for no more than 1 year, and have not received any previous medical treatment. Additionally, participants must have an HbA1c level of 7.5–10% at screening, as assessed by a local laboratory and at the pre-randomization visit, as assessed by a central laboratory, and a body mass index (BMI) between 19 and 40 kg/m² at screening.

Patients were excluded from the study if they met any of the following exclusion criteria: (1) congestive heart failure of New York Heart Association (NYHA) class III or IV or major cardiovascular events within 6 months before screening (significant cardiovascular history within the past 6 months prior to screening was defined as myocardial infarction, coronary angioplasty or bypass graft(s), valvular disease or repair, unstable angina pectoris, transient ischemic attack, or cerebrovascular accident). (2) Clinically apparent hepatobiliary disease, including but not limited to chronic active hepatitis and/or severe hepatic insufficiency. Alanine transaminase (ALT) or aspartate transaminase (AST), > 3x the upper limit of normal (ULN), or serum total bilirubin (TB) >34.2 μmol/L (2 mg/dL). (3) Estimated glomerular filtration rate (eGFR) < 45 mL/min per 1.73 m². (4) Diagnosis or history of acute metabolic diabetic complications, such as ketoacidosis and hyperglycemic hyperosmolar state, or diabetes insipidus within the past 6 months. (5) For women only, current pregnancy (confirmed by a positive pregnancy test) or breastfeeding. (6) Participation in any other study that included drug treatment in the past three months before enrollment. (7) Known hypersensitivity to dapagliflozin, metformin, or any of the excipients of the product. (8) Diagnosis or history of: a) chronic pancreatitis within the past 6 months or idiopathic acute pancreatitis within the past 4 weeks; b) gastrointestinal disease, for example, gastroenterostomy, enterectomy, Roemheld syndrome, severe hernia, intestinal obstruction, intestinal ulcer within the past 6 months; c) genetic galactose intolerance, LAPP lactase deficiency, and glucose-galactose malabsorption; d) organ transplantation or acquired immunodeficiency syndrome (AIDS) within the past 6 months; e) alcohol abuse or illegal drug abuse within the past 12 months; f) laser treatment for proliferative retinopathy within 6 months; g) stress condition, for example, surgery, serious trauma, etc., within the past 6 months, or planned surgery during the study period; h) chronic oxygen deficiency diseases, for example, pulmonary emphysema, pulmonary heart disease, within the past 6 months; i) type 1 diabetes mellitus (T1DM), diabetes resulting from pancreatic injury or secondary forms of diabetes, for example, acromegaly or (9) The subject being, in the judgment of the investigator, is unlikely to comply with the study protocol or has any severe concurrent medical or psychological conditions that may affect the interpretation of study results. (10) Involvement in planning and conducting the study.

This study protocol was approved by the ethical review board of Beijing Chaoyang Hospital of Capital Medical University with the certificate number of 2023-ke-772-3. This trial was registered at www.clinicaltrials.gov (NCT06327815). The trial protocol was in accordance with the SPIRIT guideline.

### Endpoints

2.3

The primary endpoint of the study was the change in HbA1c level from baseline after 24 weeks of treatment. The secondary endpoints included the following: (1) The proportion of patients achieving HbA1c below 7.0%, absolute change in fasting plasma glucose/postprandial glucose (FPG/PPG) from baseline to week 24, and (2) the difference in satisfaction scores between the two groups measured using the diabetes treatment satisfaction questionnaire (DTSQ) at week 24. (3) Change from baseline in the diabetes quality of life (DQOL) questionnaire scores at weeks 12 and 24. (4) The differences in patient medication usage between the two groups were measured with adherence to refills and medications scale for diabetes (ARMS-D) at week 24. (5) Adverse events (AE), serious adverse events (SAE), and adverse drug reactions (ADRs). (6) Vital signs. (7) Physical examination. (8) Clinical laboratory indices. (9) Electrocardiogram

In the exploratory substudy, the primary exploratory endpoint was the proportion of time in the tight target range (TITR, 3.9-7.8 mmol/L). Secondary exploratory endpoints included time in range (TIR, i.e., the percentage of readings and time that a person spends with their blood glucose levels in a target range of 3.9–10 mmol/L), time below range (TBR, i.e., the percentage of readings and time that a person spends with their blood glucose levels below the target range), time above range (TAR, i.e., the percentage of readings and time that a person spends with their blood glucose levels above the target range), mean amplitude of glycemic excursions (MAGE, the mean blood glucose values exceeding one standard deviation (SD) from the 24‐hour mean blood glucose, which is used as an index of glycemic variability), and standard deviation of blood glucose (SDBG), which reflects the amount of variation or dispersion of a series of glucose values.

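### MAGE is defined as a mean of glucose values, not of excursion amplitudes, so as written it mixes glucose level with variability

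*Protocol article*

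**What the plan says.** Section 2.3 (Endpoints) of the protocol article lists the CGM sub-study endpoints. TITR is the primary exploratory one. The secondary exploratory list contains TIR, TBR, TAR, MAGE and SDBG. The MAGE entry explains the endpoint as "the mean blood glucose values exceeding one standard deviation (SD) from the" 24-hour mean blood glucose, and adds "which is used as an index of glycemic variability".

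The next entry is "standard deviation of blood glucose (SDBG), which reflects the amount of variation or dispersion of a series of glucose values". MAGE and SDBG are the only two entries that describe variability; the others are proportions of time in, below or above a range.

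The Abstract gives the aim of the sub-study: "Continuous glucose monitoring will also be used to evaluate the benefits of FDC compared with co-administration on glycemic variability".

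Nothing elsewhere in the article restates or corrects the MAGE definition. Table 1 names only TITR, TIR, TAR and TBR as CGM indices. Section 2.7 (Statistical analysis) says only that all exploratory outcomes receive point estimates and 95% confidence intervals, within and between groups.

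**The concern.** The name and the definition describe different quantities. The name, "mean amplitude of glycemic excursions", calls for an average of differences: how far glucose travels from a nadir to a peak or back. The definition calls for an average of glucose readings, selected because they lie more than 1 SD from the mean. It contains no peak, no nadir and no difference.

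A variability index should not change when every reading is raised by the same amount. An average of selected readings does. If mean glucose differs between the arms at week 12, that difference passes straight into the quantity labelled MAGE and could be read as an effect on variability. CGM is performed only at week 12 (section 2.1 and Table 1), so there is no CGM baseline against which a level difference would show up.

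This is not a detail left to a fuller document. The article chose to define the endpoint, and the definition it gives is wrong.

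**Working it through.** **The plan's own figure first.** The only numbers given for the sub-study are its sample size (section 2.6), which rests on TITR: difference 10%, SD 30%, two-sided alpha 0.05, power 80%. The normal approximation gives 142 per arm. The noncentral t gives power 0.799 at 142 and 0.802 at 143, hence 143. Allowing for 20% dropout, 143 / 0.8 = 178.75, so 179 per arm and 358 in total. The stated figures reproduce, and none depends on how MAGE is defined.

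**Effect of adding a constant, by algebra.** Let g be the readings, m their 24-hour mean and s their SD. As written, the statistic W is the average of those g with |g − m| > s. Replace every g by g + c. Then m becomes m + c, s is unchanged, the same readings are selected, and W becomes W + c. A peak-to-nadir difference is unchanged, because c cancels. So W depends on level whatever the shape of the profile.

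**Illustrative profiles.** These are assumptions, not trial data: 24 hours of readings every 5 minutes, a flat baseline, and three Gaussian meal peaks (at 8, 13 and 19 h, each with SD 1 h). Amplitude MAGE is the mean of the nadir-to-peak rises exceeding 1 SD; counting peak-to-nadir falls gives the same values here. All figures are in mmol/L.

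| Baseline | Peak height | Mean | SD | As written | Amplitude MAGE |
|---|---|---|---|---|---|
| 6 | 3 | 6.94 | 1.06 | 8.66 | 2.89 |
| 8 | 3 | 8.94 | 1.06 | 10.66 | 2.89 |
| 10 | 3 | 10.94 | 1.06 | 12.66 | 2.89 |
| 6 | 5 | 7.57 | 1.76 | 10.43 | 4.82 |

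- *Level.* In the first three rows the variability is identical. The as-written statistic rises by 2.00 for each 2 mmol/L of baseline; the amplitude does not move.
- *Ranking.* Baseline 8 with peaks of 3 scores 10.66, above the 10.43 for baseline 6 with peaks of 5. The amplitudes, 2.89 against 4.82, are in the opposite order.

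In all four rows no reading lies below m − s, so it makes no difference whether the definition is taken to cover both tails or only high values.

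**How much spread the statistic still carries.** With the baseline held at 6:

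- peaks of 1.5: 7.33 − 6.47 = 0.86 above the mean;
- peaks of 3: 8.66 − 6.94 = 1.72 above the mean;
- peaks of 5: 10.43 − 7.57 = 2.86 above the mean.

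The gap grows in proportion to peak height. The statistic is therefore level plus a spread-dependent part.

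**The symmetric special case.** For a sine wave with both tails averaged, highs and lows cancel. Swings of ±1, ±2 and ±3 around 8 all give 8.0, while peak minus nadir is 2, 4 and 6. If only high values count, the selected part of the wave averages 0.90 of the half-swing. A ±2 swing then gives 7 + 1.8 = 8.8 around a mean of 7, and 9 + 1.8 = 10.8 around a mean of 9, with peak minus nadir 4.0 in both.

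**The case against.** The strongest reply is that the phrase is a short gloss in an endpoint list, not an algorithm. The endpoint carries its established name, the gloss keeps the 1-SD threshold and the 24-hour reference, and it may be shorthand for excursions above 1 SD. The neighbouring glosses are informal too. The article condenses a fuller document, and nothing in it shows that MAGE will be programmed from this sentence. All of that is fair, and it limits what can be said about the eventual analysis. It does not make the printed definition right. Even a generous reading, averaging the distances from the mean rather than the values, gives 1.72 in the three rows with 3 mmol/L peaks. That is free of level but is not the 2.89 of the excursion amplitude.

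A reader might go further and infer that the as-written statistic simply returns or duplicates mean glucose. The text does not support that. The two coincide only for symmetric profiles with both tails averaged. On meal-peak profiles the statistic lies 0.86 to 2.86 mmol/L above the mean and carries information about spread.

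The impact is also small, and this stands. MAGE is one of several secondary exploratory endpoints. The plan states no test or decision rule for it. SDBG sits beside it, is correctly described, and would show a conflict. How days are combined can properly be left to a fuller document, so its absence here is not a fault.

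**Conclusion.** The definition of MAGE in section 2.3 is wrong as written: it contradicts both the endpoint's name and its stated use. Taken literally, it yields a mixture of glucose level and spread that moves one-for-one with level and can order profiles wrongly. The dependence on level follows by algebra for any profile. The particular values (8.66, 10.66 and 12.66 against a constant 2.89) rest on the assumed meal-peak profiles and only illustrate it.

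A reader might infer that the sub-study will produce a false claim about variability. The article does not establish that. It would require the sentence to be programmed literally, the arms to differ in glucose level, and the result to be read apart from SDBG. What is supported is that such a misreading is possible and easily prevented. The consequence is confined to one secondary exploratory endpoint of the CGM sub-study. The primary HbA1c endpoint, TITR, SDBG and both sample sizes are untouched.

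**What to change.** Replace the parenthetical definition with one sentence: MAGE is the mean of the absolute differences between consecutive glucose peaks and nadirs (peak-to-nadir or nadir-to-peak), counting only excursions larger than 1 SD of that patient's 24-hour glucose values. Confirm that the program or CGM software used for the analysis computes this quantity. If the full protocol or analysis plan already defines MAGE this way, only the published wording needs correcting.

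The cost is one sentence and one check of the program. No new data are needed, and no sample size, power or alpha changes.

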### Randomization and study interventions

2.4

Patients were centrally randomized (1:1) to one of the two treatment groups using an Interactive Response Technology/Randomization and Trial Supply Management (IRT/RTSM). Prior to the study initiation, contact information and login directions for the system were provided to each site. Following randomization, patients in the FDC group received a single tablet containing 10 mg of dapagliflozin and 1000 mg of metformin hydrochloride XR once daily. Patients in the co-administration group received one tablet of 10 mg dapagliflozin once daily, and metformin hydrochloride XR, administered as two 500 mg tablets once daily with meals, or as one 500 mg tablet twice daily with meals if the patient is intolerant to the two-tablet dose. This study did not involve dose adjustments for study medications. The duration of treatment was 24 weeks.

The rescue treatment criteria from week 4 to week 12 were based on an FPG level exceeding 13.32 mmol/L, confirmed by a second measurement 3–5 days later. The rescue treatment criteria from weeks 12 to 24 were based on an FPG level exceeding 11.10 mmol/L (23). Rescue medications include but are not limited to metformin, GLP-1 receptor agonists, DPP-4 inhibitors, thiazolidinediones, sulfonylureas, and insulin. Patients administered rescue medications will continue to participate in the study and the results will be independently analyzed.

Subjects had to discontinue the use of prescription or over-the-counter medications (including vitamins, recreational drugs, dietary supplements, or herbal supplements) 7 days prior to the start of the study intervention (or 14 days in case the medication is a potential enzyme inducer) or 5 half-lives of the medication (whichever is longer) until the end of follow-up, unless the investigator and sponsor believe the medication will not interfere with the study. Acetaminophen/paracetamol with a dosage of ≤2 g/day was allowed at any time during the study period.

